#### **12.6.1.2 Patient Management**

- The difference between arms (Early Amyloid PET arm, the Late Amyloid PET arm, or the Free Choice arm) in the number of patients randomised to disease-modifying drug (DMD) or any other AD clinical trial at T2.
- The difference between the Early Amyloid PET arm and the Late Amyloid PET arm in number of participants with changes in the management plan (changes in or start of a new program or pharmacologic treatment) at T1 vs T2 vs T3.

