## 7.6 Withdrawal and Termination Criteria

### 7.6.1 Participant withdrawal

There are no formal withdrawal criteria for this study. During the conduct of the study, the Sponsor will review the safety data for trends and signals that would indicate the need for withdrawal of a participant.

In accordance with the Declaration of Helsinki, each participant is free to withdraw from the study at any time. Investigator(s) also have the right to withdraw participants from the study in the event of illness, adverse events (AEs), or other reasons concerning the health or well-being of the participant, or in the case of lack of co-operation.

Should a participant decide to withdraw after administration of the IMP(s), or should the investigator(s) decide to withdraw the participant, all efforts will be made to complete and report the observations up to the time of withdrawal as thoroughly as possible. A complete final evaluation at the time of the participant's withdrawal should be made and an explanation given of why the participant is withdrawing or being withdrawn from the study. The reason for withdrawal, if the participant will give one, must be noted in the electronic Case Report Form (eCRF). If the reason for withdrawal is a clinical AE, monitoring will continue until the outcome is evident. The specific event or test result(s) must be recorded in the eCRF.

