#### **7.6.2 Replacement of participants withdrawn from the study**

Participants who are withdrawn will not be replaced.

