### **12.5.3 Handling of missing values/censoring/discontinuations**

The reasons for incomplete data are many and include major protocol deviations, dropout because of study withdrawal or death, non-attendance at clinical visits, missing questionnaire items, uninterpretable images, etc.

The primary efficacy analysis will be conducted on the PPS population, which is based on complete cases.

Secondary efficacy analyses will be conducted on the FAS population. In time-to-event analyses, dropout and major protocol deviations are accounted for by censoring at the time of dropout or protocol deviation. In cross-sectional analyses and analyses of change between 2 timepoints, only complete cases will be included. Cases with a major protocol deviation before the first timepoint in the cross-sectional or change analysis will be excluded. The longitudinal mixed-effect analyses will be based on the observed cases. Data will be censored after a major protocol deviation. The underlying assumption in all analyses is that missing data are missing at random and not related to the primary outcome.

The proportion of missing data at each time point will be computed for the Early Amyloid PET, Late Amyloid PET, and Free Choice arms separately, and stratified for SCD Plus, MCI, and dementia.

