## **12.6 Secondary Analyses**

### **12.6.1 Secondary efficacy variables**

In the analyses of the secondary efficacy variables, a cross-sectional difference between arms in a secondary endpoint at T1, T2, T3, or T4 (see Table 1) will be carried out by a chi-squared test if the endpoint is dichotomous, a 2-sided *t*-test if the endpoint is normal, and Mann-Whitney test if the endpoint is categorical or continuous and non-normal. The effect of baseline characteristics such as age, gender, MMSE, etc will be studied by a linear or logistic regression model.

A difference between study arms in the longitudinal change of a secondary endpoint will be tested by means of logistic or linear regression where the first measurement is a covariate (ANCOVA analysis) and the second measurement is the outcome. Differences in longitudinal

trends between arms will also be examined by means of the mixed-effects regression model. The effects of baseline characteristics such as age, gender, MMSE, etc. will be studied by including them in the regression models.

All tests will be 2-sided and the significance level will be set at 5%. Bonferroni corrections for multiple testing will be applied when appropriate. Point estimates will be presented together with 95% Wald confidence intervals. A 95% non-parametric confidence interval will be constructed if the estimate is non-normal.

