## **12.8 Procedures for Missing, Unused and Spurious Data**

Missing values will not be substituted by estimated values, but treated as missing in the statistical evaluation. All data from all participants dosed in the study will be included in all listings, plots, summary tables, and statistical analyses when appropriate.

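### The complete-case rule at T2 covers the endpoint of entry into another AD trial, so a participant who leaves this study early to join one can be lost as an event

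*Protocol*

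**What the plan says.** Entry into a disease-modifying or other AD trial by 6 months is a stated objective (Protocol 5.4.2.2). It is a secondary endpoint in 10.1.2.2 and again in 12.6.1.2, where Early, Late and Free Choice arms are compared "in the number of patients randomised to disease-modifying drug (DMD) or any other AD clinical trial at T2".

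The analysis rules that reach it are general:

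- Section 12.6.1 sets the test for "a cross-sectional difference between arms in a secondary endpoint at T1, T2, T3, or T4": chi-squared when the endpoint is dichotomous.
- Section 12.5.3 sets the population: "Secondary efficacy analyses will be conducted on the FAS population". It then narrows it: "In cross-sectional analyses and analyses of change between 2 timepoints, only complete cases will be included". The same section lists dropout through study withdrawal among the causes of incomplete data.
- Section 12.8 rules out imputation: "Missing values will not be substituted by estimated values, but treated as missing in the statistical evaluation".
- Section 12.5.3 also states: "The underlying assumption in all analyses is that missing data are missing at random and not related to the primary outcome".

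On leaving the study, 7.6.1 says there are no formal withdrawal criteria. It asks for a final evaluation and for the reason for withdrawal, if the participant gives one. Sections 10.1.2.3 and 12.6.1.3 report withdrawals and their reasons as a separate item.

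**The concern.** Joining a drug trial is both the event to be counted and a foreseeable reason to stop attending this study. For a participant who stops before T2 because of it, the outcome causes the missing record. The complete-case rule then removes that person from the count of events and from the denominator. The arm with more entries loses more of them.

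The Early arm is a plausible candidate, because its PET result is available well before 6 months, whereas 9.6 places the Late-arm scan after the T2 visit. If so, the rule pulls the absolute arm difference towards zero on an objective the study sets out to measure.

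No scheduled data item clearly rescues the event. Table 1, the T1 list (9.4), the T2 list (9.5) and the management-plan variable (10.3.17) do not name randomisation into another trial. The reason for withdrawal is optional for the participant and is not linked to this endpoint.

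**Working it through.** **1. The plan's own figures.** The protocol gives no power or event rate for this endpoint. Section 12.7 gives power for the primary comparison only: 99.6%, 93% and 61% for differences of 20, 15 and 10 points, and 80% per stratum for 25 points. With 300 × 0.9 = 270 per arm, rates placed symmetrically about 50% (an assumption, since no control rate is stated), two-sided 5% and a continuity correction, I obtain 99.6%, 92.7% and 61.0%. With 90 per arm in a stratum and alpha 0.05/3, I obtain 79.9%. The figures reproduce. They do not decide the present point.

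**2. How the rules combine.** Take a participant randomised into a drug trial in month 4.

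| Course | Status under 12.5.3 | Counted? |
|---|---|---|
| Stays and attends T2 | complete case, if trial entry is recorded | yes |
| Leaves before T2, reason not given or not linked | not a complete case | no, and removed from the denominator |
| Leaves before T2, reason recorded | not settled, as the term is undefined for this endpoint | unclear |

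**3. Size, as an illustration.** Let p be the true entry rate by 6 months, n the number per arm, and q the share of entrants who leave before T2 and are not counted. The documents give neither p nor q, so both are assumptions. On complete cases:

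- denominator = n(1 − pq)
- observed rate = p(1 − q) / (1 − pq)
- power = Φ{(|p1 − p2| − 1.96·SE0) / SE1}, two-sided 5%, with SE0 from the pooled rate, SE1 from the separate rates, and no continuity correction

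Worked case: Early p = 0.10, Late p = 0.04, n = 300, q = 0.5, no other dropout.

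- Early: events 300 × 0.10 × 0.5 = 15; denominator 300 − 15 = 285; rate 5.3%.
- Late: events 300 × 0.04 × 0.5 = 6; denominator 300 − 6 = 294; rate 2.0%.
- Difference 3.2 points. SE0 = 0.01554, SE1 = 0.01559. Power = Φ{(0.03222 − 1.96 × 0.01554)/0.01559} = Φ(0.113), about 55%.

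| q | Early | Late | Difference (points) | Risk ratio | Power |
|---|---|---|---|---|---|
| 0 | 30/300 = 10.0% | 12/300 = 4.0% | 6.0 | 2.50 | 82% |
| 25% | 22.5/292.5 = 7.7% | 9/297 = 3.0% | 4.7 | 2.54 | 71% |
| 50% | 15/285 = 5.3% | 6/294 = 2.0% | 3.2 | 2.58 | 55% |
| 75% | 7.5/277.5 = 2.7% | 3/291 = 1.0% | 1.7 | 2.62 | 32% |

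**4. Range over other assumptions** (power at q = 0, 25, 50, 75%).

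- 8% vs 3%, 300 per arm: 77, 65, 49, 28%.
- 10% vs 5%, 270 per arm (the 10% withdrawal of 12.7 taken off first): 60, 49, 36, 21%.
- 3% vs 2%, 300 per arm: 12% already at q = 0, so the rule would matter little.
- 10% vs 4%, 300 per arm, with only 10% of entrants leaving: 82% falls to 78%.

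These are pairwise Early versus Late comparisons with the same q in both arms. The endpoint itself names three arms.

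**The case against.** The strongest reply is that the protocol does not make entrants leave. Section 7.6.1 has no formal withdrawal criteria, 8.6 places no restriction on concomitant medication, and the investigational-product exclusion in 7.4 applies at entry. Listing trial entry as an endpoint is compatible with entrants staying in follow-up. This stands. A reader might infer that everyone who joins another trial is dropped, or that missing at random fails by construction. The documents support neither: both depend on entrants leaving before T2 and not being counted.

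Second, a leaver need not be an incomplete case. The endpoint is a status, and once the participant is known to have been randomised elsewhere its value is known. Section 12.10 includes all randomised participants unless otherwise specified, and 7.6.1 asks for a final evaluation and a reason. This stands in part. It shows that the event may be known, but not that it will be counted. Section 12.5.3 does specify otherwise, names withdrawal as a source of incomplete data, and does not say that a recorded reason supplies the endpoint. The content of the final evaluation is not stated.

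Third, the detail could be left to the SAP. For the derivation of the endpoint that is fair. But the complete-case rule is fixed in the protocol itself, and a later analysis plan cannot recover a fact that was never collected. Table 1 is a schedule and not the eCRF, and 10.3.26 permits other data, so the absence of a named item does not prove that entry goes unrecorded.

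Fourth, the magnitude rests on assumed inputs. This stands in full. With equal departure shares the risk ratio is also nearly unchanged, so it would be wrong to infer that the relative effect shrinks.

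**Conclusion.** The concern holds as a conditional one. The T2 trial-entry endpoint falls under a complete-case rule with no exception, and no scheduled item names the event. A participant who leaves before T2 because of the event can therefore disappear from numerator and denominator, and for such participants the stated missing-at-random assumption is not tenable. Where this happens, the absolute arm difference and the power fall.

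The size cannot be derived from the protocol. It depends on the entry rates, on the share of entrants who leave, and on whether their reason is recorded and used. If no entrant leaves, nothing is lost. If half leave uncounted, an assumed difference of 6.0 points reads as 3.2 and power falls from 82% to about 55%. This is one unpowered secondary endpoint and the primary analysis is not touched, but the correction is cheap enough to be worth making.

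**What to change.** - Define the endpoint as randomisation into any AD trial, disease-modifying or other, at any time from baseline to 6 months, whatever the later participation in this study.
- Use all randomised participants as the denominator, and exempt this endpoint from the complete-case rule in 12.5.3.
- Record trial entry (yes/no and date) at T1, at T2 and on the withdrawal form, so that a leaver's status is captured in the same way in every arm.

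The cost is one extra eCRF field on existing forms and two sentences of protocol text, with no extra visit. The drawback is that participants lost with unknown trial status must be either counted as non-events or examined in a sensitivity analysis. The choice should be stated in advance.

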#### **12.6.1.3 Health Economics Objectives**

- The impact on patient-reported outcomes (cognition, anxiety, depression, coping skills, and quality of life) at T3 vs T2 vs T0 in each arm
- The difference in the cost of diagnostic workup to the etiologic diagnosis with very high confidence ( $\geq 90\%$ ) in the Early Amyloid PET arm vs the Late Amyloid PET arm. (In those centres where the participants in the Early Amyloid PET arm receive a diagnostic workup in addition to clinical evaluation before baseline, the relative costs will not be considered if the results of those exams are not known by the managing physician before the managing physician makes the etiologic diagnosis.)
- The difference between arms (Early Amyloid PET vs Late Amyloid PET vs Free Choice) in the use of medical resources (not limited to diagnostic procedures, tests, visits, and hospitalisations) and programs.

- The number of patients who withdrew from the study, and the reasons for withdrawal.

#### 12.6.1.4 Quantitative Imaging Results Assessment

PET images will be analysed centrally for quantitative imaging endpoints, as follows:

- Descriptive analysis of local visual assessment results
- The distributions and mean standardised uptake value ratio (SUVR) of the composite cortical brain regions, and converted to the centiloid scale, across amyloid PET tracers and by diagnostic subgroup.
- The distributions and mean SUVR of defined brain regions across amyloid PET tracers and by diagnostic subgroup.
- For each of the amyloid PET tracers, the composite cortical quantitative uptake (SUVR and SUVR converted to the centiloid scale) versus the local site visual reading interpretation and classification confidence.

For participants in the Early Amyloid PET Imaging arm who have a second amyloid PET scan:

- The distributions and mean change in standardised uptake value ratio (SUVR) of the composite cortical brain regions, and converted to the centiloid scale, across amyloid PET tracers and by diagnostic subgroup.
- The distributions and mean change in SUVR of defined brain regions across amyloid PET tracers and by diagnostic subgroup.
- The difference in amyloid load between the first and the second amyloid PET scan, as indicated by quantitative image assessments, will be tested with a paired data *t*-test. Data will be log-transformed if non-normal.

A SCD-specific sub-study aiming at investigating the impact of PET-amyloid result disclosure will be performed on the SCD participants. This specific protocol is submitted separately as an AMYPAD DPMS sub-study.

### 12.6.2 Safety variables and analyses

#### 12.6.2.1 Adverse events

- The number and percentage of participants with 1 or more AEs within 48 hours of drug administration will be summarised for the Safety Analysis Set and separately by gender, age, study arms, and strata (SCD plus, MCI, and dementia) and by IMP ( $[^{18}\text{F}]$ florbetaben vs  $[^{18}\text{F}]$ flutemetamol).
- A difference among the 3 study arms and between Early and Late Amyloid PET arms in number of AEs at 48 hours after IMP administration will be tested by means of a chi-squared test with significance level of .05. The analysis will be repeated for the safety end-point SAEs at 30 days after IMP administration.

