## 6.4 Risks and Benefits to Participants

### 6.4.1 Potential risks

This Phase 4 study uses radiopharmaceutical products whose safety and efficacy were established in Phase 1 to Phase 3 studies.

The potential risk of amyloid PET imaging is exposure to radioactivity from the tracer ( $[^{18}\text{F}]$ florbetaben or  $[^{18}\text{F}]$ flutemetamol). However, the tracer doses planned in this study are very low, and only 300 out of 900 patients will receive a maximum of 2 doses within 12 to 18 months. Dosimetry data derived from animals and humans indicate that potential radiation risks associated with studies using  $[^{18}\text{F}]$ florbetaben or  $[^{18}\text{F}]$ flutemetamol are low and comparable to those of other radio tracers [\[NeuraCeq™ SmPC\]](#)[\[Vizamyl SmPC\]](#). Specifically for this study, a maximum radiation dose of 6.1mSv/year will be administered. This ionizing radiation exposure is acceptable for the included subjects. The reasoning behind this is that, according to ICRP guidelines, the relative detriment for adults over 50 years of age is one fifth or one tenth of the 6.1mSv, the latter being based on radiation exposure of the whole population. As such, the relative dose for detriment assessment (corrected to adult dose) for a subject is between 0.61 and 1.22mSv, which is category IIa to IIb risk level for the volunteer. According to ICRP guidelines this is justified if the level of societal benefit is intermediate to moderate, which is the case of this study.

The recommended activity for an adult is 300 MBq ( $\pm 20\%$ ) for  $[^{18}\text{F}]$ florbetaben [\[NeuraCeq™ SmPC\]](#) and 185 MBq ( $+10\%$ ) for  $[^{18}\text{F}]$ flutemetamol [\[Vizamyl SmPC\]](#).

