## **9.9 T4: Follow-up Visit for Participants in Early Amyloid PET Arm**

In a follow-up assessment, the participants who were randomized to the Early Amyloid PET arm will receive an optional second amyloid PET imaging scan 12 to 18 months after the first scan. All female participants of childbearing potential must have a negative pregnancy test before the imaging study is done. Concurrent medications will be reviewed before imaging.

The following will be recorded within 28 days after the optional second scan, for all participants who have undergone the second amyloid PET scan:

- Amyloid PET scan results
- All AEs that occur within 48 hours of study drug administration
- All SAEs occurring within 30 days of study drug administration

The following will be recorded for all participants in the Early Amyloid PET arm:

- Managing physician's etiologic diagnosis after review of amyloid PET imaging results
- Managing physician's management plan after review of amyloid PET imaging results

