### **10.2.3 Adverse event and serious adverse event reporting**

All AEs should be recorded using acceptable diagnoses, if possible. If an AE has already been reported it is not necessary to report each individual sign and symptom of that AE as a separate AE. For example, if myocardial infarction is reported as an AE, there is no need to report elevated creatine kinase and abnormal ECG, or other related signs, symptoms, or laboratory values as separate AEs. However, if both occurred in isolation and myocardial infarction was not diagnosed, then each event would be reported as an AE.

The intensity of all AEs will be graded as mild, moderate, or severe using the following definitions:

|           |                                                                      |
|-----------|----------------------------------------------------------------------|
| Mild:     | Tolerable.                                                           |
| Moderate: | Interferes with normal activity.                                     |
| Severe:   | Incapacitating (causes inability to perform usual activity or work). |

The investigator will be instructed to closely monitor each participant who experiences an AE (whether ascribed to the IMP or not) until the outcome of the AE has been determined.

In addition to the investigator's own description of the AEs, each AE will be encoded by the Sponsor/CRO according to a well-recognised dictionary of medical codes.

SAEs will be recorded in the eCRF if they occurred as follows:

- After a participant first received an IMP and throughout the participant's follow-up period\*, whether or not considered related to the IMP, and
- After the participant's follow-up period, and for which a causal relationship to the IMP cannot be ruled out.

(\*Follow-up period is defined as the protocol-stipulated period or, for participants prematurely withdrawn from a study, the duration of a participant's participation.)

All serious and non-serious AEs must be followed for a final outcome until the end of the follow-up period. An outcome of "unknown" is not considered to be an acceptable final outcome. An outcome of "not yet resolved" is an acceptable final outcome for non-serious AEs at the end of a participant's participation in a study, and for SAEs at database lock.

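### The between-arm AE test is not limited to the first injection, so equal per-injection risk can appear as a safety difference against the Early PET arm

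*Protocol*

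**What the plan says.** Section 12.6.2.1 has two parts. The first is descriptive and counts participants with at least one AE within 48 hours, in the Safety Analysis Set. The second is a test, and what it compares is given as "A difference among the 3 study arms and between Early and Late Amyloid PET arms in number of AEs at 48 hours after IMP administration". The method named there is chi-squared, at the 0.05 level. The same section then extends the plan to serious events: "The analysis will be repeated for the safety end-point SAEs at 30 days after IMP administration". The synopsis repeats this plan.

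The number of injections differs by arm:

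- **Early:** one within 4 weeks of baseline and an optional second 12 to 18 months later (Sections 6.1.1 and 6.1.2). Section 6.4.1 says that "only 300 out of 900 patients will receive a maximum of 2 doses within 12 to 18 months".
- **Late:** one, at about 8 months (Section 9.6).
- **Free Choice:** none or one, as the managing physician decides (Section 6.1.1).

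Section 9.9 has AEs and SAEs recorded after the second scan as well. The Safety Analysis Set in Section 12.2 takes in anyone dosed and has no first-dose limit. The protocol gives no expected AE rate and no expected uptake of the second scan.

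**The concern.** A between-arm safety test should compare groups that had the same opportunity to show an event. Here only the Early arm can contribute two 48-hour windows and two 30-day windows per participant. If the risk per injection is identical everywhere, the Early arm still accumulates more events, and the test can reject because more injections were given. The distortion runs in one direction only, against early PET, which is the strategy that the trial evaluates.

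The unit is also unclear. The descriptive summary counts participants and the test refers to a number of AEs. A chi-squared test needs independent units in a defined denominator. Events do not meet that when one person can have several, or can have events after each of two injections.

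**Working it through.** **Plan's own figure.** The protocol states no power, rate or error figure for the safety test, so there is none to reproduce. Its only stated power figures, in Section 12.7, concern efficacy.

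**Inputs from the protocol.** 300 participants per arm (Section 6.1.1: 100 in each of 3 strata). Chi-squared test at 0.05 (Section 12.6.2.1). Section 12.6.1 says for the secondary efficacy tests "All tests will be 2-sided and the significance level will be set at 5" percent; a chi-squared test is non-directional in any case.

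**Assumed inputs.** Risk q of at least one AE per injection, the same in all arms, from 1% to 10%. Uptake u of the second scan, from 25% to 100%.

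**Formulas.** A Late participant has risk q. An Early participant has on average q + u·q·(1−q). The difference, u·q·(1−q), is never negative, so the bias cannot favour Early. The normal approximation to the rejection probability is Φ[(d − 1.96·se0)/se1], where d is the difference, se0 the pooled and se1 the unpooled standard error.

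**One cell by hand (q = 5%, u = 50%).**

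- Early risk = 0.05 + 0.5 × 0.05 × 0.95 = 0.07375, so d = 0.02375.
- Pooled proportion = (0.07375 + 0.05)/2 = 0.061875; se0 = √(0.061875 × 0.938125 × 2/300) = 0.01967.
- se1 = √[(0.07375 × 0.92625 + 0.05 × 0.95)/300] = 0.01965.
- (0.02375 − 1.96 × 0.01967)/0.01965 = −0.75, which gives about 23%.

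**All cells.** Simulation with 200,000 replicates, injections independent, endpoint of participants with at least one AE, Early versus Late. The normal approximation is in brackets.

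| Risk per injection | Uptake 25% | Uptake 50% | Uptake 100% |
|---|---|---|---|
| 1% | 5.4% (4.7%) | 7.5% (7.9%) | 15.7% (16.8%) |
| 2% | 6.9% (6.0%) | 12.0% (11.7%) | 29.3% (29.1%) |
| 5% | 9.8% (9.2%) | 23.1% (22.6%) | 61.5% (60.5%) |
| 10% | 14.0% (13.9%) | 39.2% (39.0%) | 88.6% (88.1%) |

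With no second scans the rate is about 5%.

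**Variations.**

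- 270 per arm, applying the 10% withdrawal of Section 12.7: 6.6%, 11.1% and 26.8% at 2% risk; 9.1%, 20.6% and 56.8% at 5%.
- Comparing event totals instead of participants, with at most one AE counted per injection: 9.3%, 22.4% and 61.8% at 5% risk. Several AEs after one injection were not modelled.
- Three-arm test among dosed participants, with every Free Choice participant scanned: 6.4%, 11.7% and 30.8% at 2% risk; 9.3%, 22.6% and 65.5% at 5%.

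**After the fix.** Restricting the comparison to the first injection gives 4.5% to 5.1% across the assumed risks and uptakes.

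**The case against.** Four points can be made for the plan.

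- **The singular wording may mean the first injection, and the SAP may settle it.** Section 12.6.2.1 speaks of administration in the singular, and the second scan has its own section. But Section 9.9 uses an equivalent phrase for AEs after the second scan, so the wording does not exclude them. The protocol already fixes comparison, variable, test and level. A SAP could repair this, but the protocol as written does not.
- **The unit may just be loosely worded.** The adjacent summary counts participants, and Section 12.6.1 assigns the chi-squared test to dichotomous endpoints. A participant-based test may well be what was meant, and the table above assumes it. This part of the point is a request for clarity. The exposure imbalance remains under either unit.
- **The inflation may be modest.** This stands in part. The second scan is optional, comes at least a year later and needs fresh consent (Sections 7.3 and 13.4.2), and Section 6.2 describes a favourable safety profile. At 1% to 2% risk and 25% to 50% uptake the false-positive rate is only about 5% to 12%.
- **The consequence is limited.** This stands. The test is secondary, no interim analysis is planned (Section 12.9) and no formal termination criteria use it (Section 7.6.3).

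A reader might also infer that the SAE comparison rests on inconsistent data. Sections 10.2 and 10.2.2 record SAEs within 30 days of dosing. Section 10.2.3 records them "After a participant first received an IMP and throughout" the follow-up period. In Section 9.9, "The following will be recorded within 28 days after the optional second scan" introduces a list that includes "All SAEs occurring within 30 days of study drug administration". These passages do not agree, but the tested SAE endpoint is fixed at 30 days, so wider collection does not change it. SAE reporting also does not wait for the T4 record, because investigators must report within 24 hours of learning of an event (Section 10.2.3). The documents therefore do not show lost SAEs or an altered test.

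**Conclusion.** The point holds: followed as written, the test compares arms with unequal numbers of injections, and any resulting bias runs against Early PET. The Early versus Late false-positive rate lies between about 5% and 89% over the assumed grid of 1% to 10% risk per injection and 25% to 100% uptake.

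A reader might infer that a false safety signal is likely. The documents do not support that, because they state neither quantity that determines it. Rates around 40% or more need roughly 5% risk with 75% uptake (42.0%) or 10% risk with about half taking the second scan (39.2%). For rare 30-day SAEs the inflation would be small; no SAE rate is given and none was modelled. The primary endpoint is not touched. The change should be made because the protocol has no safeguard and the remedy is cheap, but it does not threaten the trial's main conclusion.

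**What to change.** In Section 12.6.2.1 and the safety part of the synopsis, define the between-arm test as the proportion of dosed participants with at least one AE within 48 hours of the **first** administration, and likewise for SAEs within 30 days of the first administration. Naming participants as the unit removes the mismatch with the descriptive summary. Summarise AEs and SAEs after the second scan separately, per administration.

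The cost is a wording change in the protocol, carried into the SAP, with no added participants, visits or data. The small downside is that second-scan events are described and not tested.

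As a separate, minor matter, reconcile the SAE collection windows in Sections 9.9, 10.2.2 and 10.2.3 so that sites work from one rule.
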